### 2.3. Exclusion Criteria

(1) those who have been diagnosed with other causes of chronic coughs, such as chronic respiratory diseases (chronic obstructive pulmonary disease, bronchial asthma, bronchiectasis, interstitial lung disease, pulmonary tuberculosis, etc.), gastroesophageal reflux disease, chronic sinusitis, and allergic rhinitis within the last 2 years

(2) those who have the following symptoms that can be presumed to cause cough: wheezing, chest tightness, dyspnea, runny nose, nasal congestion, sneezing, postnasal drip, abnormal findings in the ear canal, heartburn, reflux, fever, and hemoptysis

(3) those with abnormal findings on a chest X-ray that may cause cough 

(4) those with abnormal findings in the pulmonary function tests

(5) those with wheezing, rales, postnasal drip, or cobblestone throat during the physical examination

(6) those who have been diagnosed with an acute respiratory disease within the last 4 weeks

(7) those who are current smokers, quit smoking within 3 months, or have a history of excessive smoking in the past 30 pack years or more

(8) those who are taking angiotensin-converting enzyme (ACE) inhibitors or dipeptidyl peptidase-4 (DPP-4) inhibitors or have taken them within the last 4 weeks

(9) those who have taken antitussives, expectorants, steroids, anti-leukotrienes, anticholinergics, long-acting beta 2 agonists (LABA), oral antihistamines, or any herbal medicine within the past 2 weeks

(10) those who have been diagnosed with a malignant tumor within the last 5 years

(11) those with severe liver or renal disease (aspartate aminotransferase (AST) or alanine aminotransferase (ALT) levels ≥ 3 times the upper limit of normal or creatinine levels ≥ 2 times the upper limit of normal) 

(12) those with a history of serious alcohol or drug abuse 

(13) women of childbearing age who are pregnant or lactating or who do not agree to use an effective method of contraception during the trial period

(14) those with genetic problems such as galactose intolerance, Lapp lactase deficiency, or glucose-galactose malabsorption

(15) those with known hypersensitivity to the investigational products 

(16) those who had taken other investigational products within 3 months 

(17) those who have not recorded a cough diary for at least 7 days immediately prior to the baseline visit

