### 2.7. Sample-Size Calculation

This is the first exploratory clinical trial to evaluate the feasibility and preliminary effect of *Maekmundong-tang* administration in patients with nonspecific chronic cough. Therefore, there are no prior literature references for sample size calculation. Referring to a study that recommended a minimum of 12 people per group in a preliminary study in the field of life sciences [28], a total of 24 participants, with 12 participants per group, are needed. Considering a dropout rate of 20%, a total of 30 participants, 15 in each group, were specified as the target sample size.

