All statistical analysis is based on a two-sided test, and the significance level is set at 0.05. For continuous data, the mean and confidence interval are presented, whereas for categorical data, the frequency and percentage are presented. Statistics on the demographic and socioeconomic characteristics are presented for each group. Depending on normality, continuous data are analyzed using the independent *t*-test or Wilcoxon rank sum test, whereas categorical data are analyzed using the chi-square or Fisher’s exact test. For analyzing the effectiveness outcomes, the mixed-effect model repeated-measures method will be used, with each group and visit as the fixed factor and the participants as the random factor. If necessary, variables that show statistical differences in demographics or variables that can affect chronic cough will be set as fixed factors and analyzed. Intragroup differences in values before and after treatment will be analyzed, based on normality, with the Student’s paired *t*-test or Wilcoxon signed rank test. The IMOS and IMPSS scores are analyzed using Fisher’s exact test. The repeated-measures analysis of variance method is used to compare the difference in trend change between groups for the effectiveness outcomes, and Dunnett’s procedure is used for correction of the multiple-comparison analysis. If necessary, subgroup analysis will be performed by categorizing the participants according to their baseline characteristics (chronic cough pattern identification [29], presence of yin deficiency [27], sex, age, etc.). For the analysis of safety outcomes, the chi-square or Fisher’s exact test will be performed to compare the number of adverse events in the study groups. In addition, AST, ALT, BUN, creatinine, and vital signs will be analyzed using a paired *t*-test or Wilcoxon signed rank test to determine differences from before to after treatment. No interim analysis has been planned. All statistical analyses will be performed by a statistician, independently of trial procedure, by using the statistical program SAS^®^ Version 9.4 (SAS Institute Inc., Cary, NC, USA). 

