As this study aims to evaluate the feasibility of a large-scale study of *Maekmundong-tang* for nonspecific chronic cough, various feasibility outcomes, including the recruitment, adherence, and completion rates, were set as study feasibility measures by referring to the Consolidated Standards of Reporting Trials (CONSORT) 2010 statement for randomized pilot and feasibility trials [16]. We will evaluate the effects of *Maekmundong-tang* and *Saengmaek-san* on cough severity, frequency, and quality of life through outcome measures, including CSS, cough VAS, and LCQ. In addition, as *Maekmundong-tang* is widely used for paroxysmal cough caused by bronchial hypersensitivity in clinical practice [9], symptoms related to cough hypersensitivity will be explored using HARQ. *Maekmundong-tang* might normalize the production and gene expression of airway mucin that is observed in various respiratory diseases and is accompanied by yin deficiency [39]. Therefore, we will examine the change of yin deficiency using the yin deficiency pattern-identification questionnaire. In addition to the self-reported questionnaire, we will measure changes in serum biomarkers, including eosinophils, total IgE, and plasma fibrinogen [40], to determined the underlying mechanisms of *Maekmundong-tang* and *Saengmaek-san* action for improving cough.

According to a systematic review summarizing the effects of *Maekmundong-tang* on patients with cough, 4 of the 9 included RCTs reported adverse events [9]. Among them, rash (1 case) and elevation of alkaline phosphatase (2 cases) were related to *Maekmundong-tang* [9]. According to a randomized comparative clinical trial wherein *Saengmaek-san* (modified formula) was administered for 7 days to patients with postinfectious cough, no adverse events, such as fatigue, dry throat, or globus sensation, occurred in the *Saengmaek-san* group on follow-up after 3 months [37]. Therefore, based on these previous studies, we will prioritize the safety of participants by systematically monitoring adverse events after the administration of *Maekmundong-tang* and *Saengmaek-san*, and will evaluate their safety profiles. If an adverse event occurs during the clinical trial period, it will be followed up by the researcher until it disappears.

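### The named safety analyses are significance tests with almost no power at 12 to 15 per arm, and the only one named for laboratory values tests an average shift that masks large rises in a few participants

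*Protocol article*

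**What the plan says.** Section 2.8 of the protocol article names two safety analyses. For laboratory values and vital signs it is a before/after test: "AST, ALT, BUN, creatinine, and vital signs will be analyzed using a paired *t*-test or Wilcoxon signed rank test to determine differences from before to" […]. For adverse events, "the chi-square or Fisher’s exact test will be performed to compare the number of adverse events in the study groups". The same section sets the general rule: "All statistical analysis is based on a two-sided test, and the significance level is set at 0.05". It also has continuous data summarised by a mean and confidence interval, and categorical data by frequency and percentage.

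Section 2.6.3 schedules AST, ALT, BUN and creatinine at screening and at Week 6. Adverse events are to be found at each visit through physical examination and participant self-report.

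Limits for individual laboratory values appear once, in exclusion criterion 11 (section 2.3), which gives them as "AST) or alanine aminotransferase (ALT) levels ≥ 3 times the upper limit of normal or creatinine levels ≥ 2 times the upper limit of normal". The safety analysis does not use them.

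On size, section 2.7 says that "a total of 24 participants, with 12 participants per group, are needed" and that "a total of 30 participants, 15 in each group, were specified as the target sample size". The Discussion says of the two medicines that the investigators "will evaluate their safety profiles".

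**The concern.** Liver or kidney injury from a medicine usually shows as a large rise in a few people, not as a small rise in everyone. A before/after test of the mean or centre is built for the second pattern and is poor at the first. One extreme value raises the standard deviation about as fast as it raises the mean, so a worse injury does not make the paired t-test more likely to be significant.

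The general reporting rules do not fill this gap. Laboratory values are continuous, so they get a mean and an interval, which carries the same inflated standard deviation. The article names examination and self-report as the routes for finding adverse events, and a rise without symptoms need not arrive by either. The paired test also leaves the randomised comparison unused.

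For adverse events the issue is simpler. At this size a p-value carries little information, and an interval would show that openly. Safety is a stated objective and the trial is meant to inform a larger one, so the form of the safety result matters.

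**Working it through.** **Inputs from the article.** Two-sided 0.05 (section 2.8). 12 per group needed, 15 per group after the dropout allowance, 1:1 allocation (sections 2.4 and 2.7). The plan's own figure reproduces: 12/(1 − 0.20) = 15 per group, 30 in total. No power or precision figure is given for safety.

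**Paired t-test, limiting case.** Let k of n participants rise by the same amount R and the rest not change. The mean change is Rk/n and the variance is R²k(n − k)/(n(n − 1)), so

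t = √[k(n − 1)/(n − k)],

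in which R cancels. Unequal rises only lower t.

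| n | k=1 | k=2 | k=3 | critical value |
|---|---|---|---|---|
| 15 | √(14/14) = 1.00 | √(28/13) = 1.47 | √(42/12) = 1.87 | 2.145 |
| 12 | √(11/11) = 1.00 | √(22/10) = 1.48 | √(33/9) = 1.91 | 2.201 |

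For n = 15 the p-values are 0.334, 0.164 and 0.082. Significance is first reached at k = 4 (t = √(56/11) = 2.26, p = 0.041).

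With noise in the other participants the bound is no longer exact. In simulations at n = 15 with assumed SDs of change of 3, 5 or 8 U/L and assumed rises of 100 or 180 U/L, the paired t-test rejected in 0 to 8% for k = 1 to 3.

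**Signed rank test.** Section 2.8 chooses between the tests by normality for before/after differences, and a few extreme rises would usually lead to this one. If the k large rises take the top ranks and the other changes are symmetric about zero, the rejection rate can be counted exactly. At n = 15 the two-sided exact test rejects upward when W+ ≥ 95. The top 1, 2 or 3 ranks supply 15, 29 or 42, and the other signs are coin tosses. Counting both tails gives 4.8%, 8.4% and 15.1%, against 4.8% with no effect at all. Simulations under assumed ALT values agree: about 5%, 8 to 9% and 14 to 16% in one set, and 4 to 6%, 9 to 11% and 16 to 19% in another with different assumptions. One severe case adds nothing to the rejection rate.

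**Adverse events, Fisher's test, k v 0 of 15.** For small k the two-sided p is 2·C(15,k)/C(30,k).

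- 1 v 0: p = 1.00
- 2 v 0: p = 0.483
- 3 v 0: 2 × 455/4060 = 0.224
- 4 v 0: 2 × 1365/27405 = 0.100
- 5 v 0: 2 × 3003/142506 = 0.042, the first significant result

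The uncorrected chi-square first reaches significance at 4 v 0 (p = 0.032). Power of Fisher's test for true rates of 20% v 0% is 16%, and for 13.3% v 0% it is 4%.

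**What counts with exact intervals would show (Clopper-Pearson 95%, n = 15).**

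- 0/15: 0 to 21.8% (upper limit 1 − 0.025^(1/15))
- 1/15: 0.2 to 31.9%
- 2/15: 1.7 to 40.5%
- 3/15: 4.3 to 48.1%

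With 0/12 the upper limit is 26.5%.

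**The case against.** The strongest reply is that the article does not plan to judge safety by p-values alone. Adverse-event occurrence and frequency are an outcome at each visit, categorical data are reported as counts and percentages, and events are followed until they resolve. No sentence says that p>0.05 will be read as safe. A reader might infer that injury in 1 to 3 participants would be reported as no difference. The documents do not support that, and the point does not rest on it.

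A second reply is that a laboratory rise may be recorded as an adverse event. The Discussion does list alkaline phosphatase elevations among adverse events in earlier trials. That is reasonable, but the article does not say it for AST, ALT, BUN or creatinine.

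A third is that threshold tables are routine detail for a full protocol or analysis plan, neither of which is shown. Their absence alone would not be a finding. The point here concerns the method that the article does name.

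A fourth is that low power follows from pilot size. This is true, and it is a reason to report intervals in place of relying on tests.

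A reader might also carry the safety tests into the insurance-coverage argument. The article ties that argument to cost-effectiveness (sections 2.9 and 4), and no safety test enters it.

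**Conclusion.** The concern holds as a matter of method. The only analysis named for AST, ALT, BUN and creatinine is a within-group test of average shift. It does not compare the arms, and it would usually be non-significant with very large rises in up to 3 of 15 participants (20% of an arm). The adverse-event test needs 5 v 0 under Fisher, or 4 v 0 under the uncorrected chi-square.

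The limiting t values and the Fisher results need no clinical assumption, except that the t values take the other participants as unchanged. The exact signed rank figures assume symmetric changes in the other participants. The simulated ranges rest on assumed ALT values and variation that are not in the documents. Kidney values were not simulated, although the t and rank arguments apply to any measurement.

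This is a cheap, optional to modest improvement, because counts of adverse events will be shown in any case and no false conclusion is planned.

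**What to change.** In section 2.8 or the analysis plan:

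1. Keep mean changes in laboratory values and vital signs as description.
2. For AST, ALT and creatinine, report by arm the number and percentage of participants with a Week 6 value at or above the limits already in exclusion criterion 11. For BUN, use the number above the normal range. Give exact 95% intervals. For AST, ALT and creatinine, eligible participants start below these limits at screening, so each count is of new crossings. The limits serve here for reporting only, not as a rule for managing participants.
3. Add a shift table by arm from baseline (the screening laboratory value) to Week 6.
4. For adverse events, report the between-arm risk difference in participants with at least one event, with an exact or score 95% interval.
5. State that a non-significant test is not evidence of safety.

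The cost is a few lines and two extra tables from data already collected, with no change to visits or sample size. The downside is that the intervals will look wide: no cases in 15 still leaves an upper limit of 21.8%.

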### 2.9. Economic Evaluation

Economic evaluation will be conducted along with the randomized controlled trial (RCT) for feasibility, effectiveness, and safety. The cost-effectiveness of *Maekmundong-tang* will be estimated compared to *Saengmaek-san*, in regard to the healthcare system and societal perspective.

Medical, non-medical (transportation, time, and nursing care costs), and productivity loss costs due to participants’ chronic cough during the trial period will be estimated using the cost questionnaires, institutional data, and if necessary, data from Statistics Korea. Especially, productivity loss will be assessed using the Work Productivity and Activity Impairment Questionnaire: General Health V2.0 [30,31]. With regard to the effectiveness data, trial outcome measures, including EQ-5D-5L/EQ-VAS, CSS, and cough VAS, will be determined and, thereby, the incremental cost–utility ratio and the incremental cost-effectiveness ratio between *Maekmundong-tang* and *Saengmaek-san* will be calculated. 

The analysis period is based on the clinical trial period, and for participants who drop out, data will be collected until the end of the administration of the investigational product for each participant. However, if an individual participant drops out due to an adverse event or intercurrent disease during the clinical trial, or due to aggravation of cough symptoms, a telephonic follow-up will be conducted at Week 24 with the consent of the participants and without being excluded from the data collection of the economic evaluation study. If necessary, one-way sensitivity analysis will be performed for possible variables, a tornado diagram will be presented, and a probability sensitivity analysis will be performed using the distribution and representative values of variables. In addition, if necessary, subgroup analysis can be performed according to the subgroup analysis plan of the trial. If the full yield cost and effectiveness outcomes of interventions during the trial period cannot be observed, a decision-analytic model will be developed to conduct a long-term evaluation. 

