For the cough VAS assessment, participants will self-evaluate their subjective discomfort based on cough severity, frequency, and urge to cough on a scale of 0 (no discomfort from coughing) to 100 (the highest discomfort imaginable) for the past 3 weeks [21]. This assessment will be undertaken at every visit, except for the screening visit, as well as during the telephonic follow-up survey (at Week 24), and will be investigated through a numerical rating scale (NRS) score from 0 to 100. The LCQ is a 19-item questionnaire designed to measure the quality of life of patients with cough and is divided into physical, mental, and social categories [22]. Each item is checked on a scale of 1 to 7, with higher scores indicating better health. The Korean version of the LCQ has been verified for validity and reliability [23]. The HARQ is a self-report questionnaire that measures cough hypersensitivity, and each of 14 questions is evaluated on a scale of 0 to 5. For normal individuals, the average score is 4 points, and the upper limit of the normal range is 13 points [24]. The IMOS is a tool for the investigator or participant to evaluate the degree of posttreatment improvement [25], and has been set as the investigator’s evaluation tool in this clinical trial. The IMPSS is an evaluation tool for ascertaining the participant’s treatment satisfaction [25]. Each tool is evaluated on a scale of 1–5 points. The EQ-5D-5L is a self-report questionnaire that is used to evaluate the quality of life, based on a 5-point scale over five areas: mobility, self-care, usual activities, pain/discomfort, and anxiety/depression [26]. The EQ-VAS asks participants to rate their own health from 0 (the worst imaginable health status) to 100 (the best imaginable health status) [26]. In case of telephonic follow-up (at Week 24), the EQ-VAS will be investigated through a 0 to 100 NRS. The Yin Deficiency Questionnaire is a pattern identification questionnaire with 27 questions, and the reliability and validity of this questionnaire have been established. Each question is evaluated on a 7-point Likert scale, of which points 1–4 are converted to 0 points and points 5–7 are converted to 1 point for calculation. The cutoff score for a yin deficiency diagnosis is 10 points [27]. The serum biomarkers include eosinophils, total immunoglobulin E (IgE), and plasma fibrinogen, which will be evaluated at the screening visit and at Week 6. In particular, during the telephonic follow-up survey (at Week 24), CSS, cough VAS, EQ-5D-5L/EQ-VAS, and cost questionnaires will be surveyed through a phone call.

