**ASSESSMENTS**						
CSS ***		●	●	●	●	●
Cough VAS		●	●	●	●	●
LCQ		●	●	●	●	
HARQ		●	●	●	●	
IMOS/IMPSS			●	●	●	
EQ-5D-5L/EQ-VAS		●	●	●	●	●
Yin Deficiency Questionnaire		●		●		
Cost questionnaire ****		●	●	●	●	●
Laboratory tests *****	●			●		
Adverse events investigation		●	●	●	●	
Compliance test			●	●		

* Including auscultation as well as nasal and throat examinations; ** Including X-ray examination of paranasal sinuses, if considered necessary by the investigator; *** Assessed by cough diary, except for the telephone survey conducted at Week 24; **** Questionnaire to record medical, non-medical (transportation, time, and nursing care), and productivity-loss costs due to chronic cough of participants; ***** Including hematological parameters, fasting blood glucose level, liver and renal function tests, electrolyte test, total IgE, and fibrinogen level. The urinary human chorionic gonadotropin level was assessed at the screening visit for only women of childbearing age. Abbreviations: CSS, Cough Symptom Score; ECG, electrocardiogram; EQ-VAS, the EuroQol Visual Analog Scale; EQ-5D-5L, a five-level version of the EuroQol Five-dimensional Descriptive System; HARQ, Hull Airway Reflux Questionnaire; IMOS, Integrative Medicine Outcome Scale; IMPSS, Integrative Medicine Patient Satisfaction Scale; LCQ, Leicester Cough Questionnaire; PICCQ, Pattern Identification for Chronic Cough Questionnaire; VAS, visual analog scale.

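### The stated cost scope is limited to chronic cough, so care for study-drug adverse events falls outside it, while the cost-utility ratio uses a generic utility measure and work loss a general-health instrument

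*Protocol article*

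**What the plan says.** Section 2.9 (Economic Evaluation) sets the comparison of the two herbal medicines "in regard to the healthcare system and societal perspective". It lists medical, non-medical and productivity costs and ties them to cough: "productivity loss costs due to participants’ chronic cough during the trial period will be estimated using the cost questionnaires". The other named sources for these costs are "institutional data, and if necessary, data from Statistics Korea". The Table 1 footnote describes the cost questionnaire in the same terms, ending with "productivity-loss costs due to chronic cough of participants". Table 1 schedules that questionnaire at five contacts: Weeks 0, 3, 6, 9 and 24.

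On work loss, the next sentence of Section 2.9 says that "productivity loss will be assessed using the Work Productivity and Activity Impairment Questionnaire: General Health V2.0".

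On effects, Section 2.9 says that "trial outcome measures, including EQ-5D-5L/EQ-VAS, CSS, and cough VAS, will be determined", and from these it will form an incremental cost-utility ratio and an incremental cost-effectiveness ratio. Section 2.6.2 describes the EQ-5D-5L by its five areas: "mobility, self-care, usual activities, pain/discomfort, and anxiety/depression".

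Section 2.9 also keeps some dropouts in the economic data to Week 24, with their consent. The rule applies "if an individual participant drops out due to an adverse event or intercurrent disease during the clinical trial", and likewise when cough worsens.

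**The concern.** In a cost-utility ratio, the costs on top and the health effects underneath should follow from the same events. Suppose a participant has a drug reaction, sees a doctor and takes a medicine for it. The EQ-5D-5L has no attribution to cough, so any loss of health from the reaction can lower that participant's utility. The consultation and the medicine are not costs of chronic cough, so they lie outside the stated cost scope. The event can then count in the effect and not in the medical cost.

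From a healthcare-system perspective, care caused by the compared drugs would normally belong in the comparison. The Discussion (Section 3) foresees such harm: it reports rash and raised alkaline phosphatase related to Maekmundong-tang in earlier trials. The Introduction, Discussion and Conclusions all tie the economic result to possible insurance coverage, so which costs are counted matters to the reader for whom the result is meant.

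The productivity wording has a related fault. Loss described as due to cough and loss measured by a general-health instrument are different quantities and can give different totals under the societal perspective.

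**Working it through.** **Figure that can be reproduced.** Section 2.9 gives no cost, utility or ratio. The only figure used below is the arm size in Section 2.7: 24 / (1 − 0.20) = 30 participants, or 12 / (1 − 0.20) = 15 per arm. This agrees with the protocol.

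**Scope of each component, side by side.**

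| Component | Stated scope | Place |
|---|---|---|
| Medical, non-medical and productivity costs | due to chronic cough | Section 2.9; Table 1 footnote |
| Productivity instrument | General Health version | Section 2.9 |
| EQ-5D-5L / EQ-VAS | generic, not attributed to cough | Sections 2.6.2 and 2.9 |
| CSS, cough VAS | cough-specific | Sections 2.6.2 and 2.9 |
| Perspective | healthcare system and societal | Section 2.9 |

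**The two ways of reading the cough phrase.**
1. It governs all three cost types. Adverse-event care is then outside the cost scope, while its health loss can enter the utility.
2. It governs productivity loss only. It then conflicts with the next sentence, which names a general-health instrument for that same loss.

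Either way the text needs correcting. The Table 1 footnote has the same structure and does not settle the matter.

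**Which ratios are touched.** The utility mismatch concerns the cost-utility ratio. The CSS and cough-VAS ratios have cough-specific effects, so they would be affected only through the omitted cost.

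**Illustration of size, on assumed values only.** Let one arm of 15 have k more treated adverse events than the other, each costing C. The omitted part of the difference in mean cost is

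kC / 15.

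- k = 2: 2C / 15 = 0.133C per participant.
- One event costing 10C: 10C / 15 = 0.667C per participant.
- k = 0 at equal unit cost: 0.

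For the cost-utility ratio, let dr be the between-arm difference in the proportion with a treated event and dQ the QALY difference, held fixed. The shift in the ratio is

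C × dr / dQ.

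- dr = 0: 0.
- dr = 0.05, dQ = 0.02: 2.5C per QALY.
- dr = 0.15, dQ = 0.005: 30C per QALY.

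None of k, C, dr or dQ is in the article. These lines show how the omission would act and are not an estimate of it.

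**The case against.** The strongest reply is that nothing in the article excludes adverse-event care. The cough phrase may be loose shorthand for the condition and its treatment. Institutional data are a second source with no cough limit of their own. Adverse events are investigated at Weeks 0, 3, 6 and 9 and followed until they disappear, so they could be costed. The items on the cost questionnaire belong to a fuller document that is not shown.

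Much of this stands. A reader might infer that the plan leaves adverse-event costs out or will not record them. The text supports only that they are outside the scope as stated. The reply does not remove the point, however. The scope is stated in two places, so this is not a detail left to another document. Institutional data are named as a source for those same costs, with no wider scope given. At Week 24, Table 1 schedules the cost questionnaire but no adverse-event investigation.

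Three stronger readings are not supported:
- A reader might say that work loss is counted from all causes. The article gives only the instrument's title, so general-health rather than cough-specific is as far as the text goes.
- A reader might say that following adverse-event dropouts to Week 24 contradicts the cost scope. It does not: the call also collects CSS, cough VAS and EQ-5D-5L/EQ-VAS, and the same rule covers dropout for worsening cough, so retention has a purpose whatever the cost scope. If anything, it suggests that the authors want these participants' outcomes counted.
- A reader might take a raised laboratory value as an example of utility lost without cost. Nothing in the article says that it would lower the EQ-5D-5L.

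Limiting costs to the disease is also partly a design choice, and it fits the two cough-specific ratios.

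**Conclusion.** The point holds in a limited form. As written, the cost scope does not reach care for study-drug adverse events, although the cost-utility ratio uses a utility measure that can carry their health loss, and the cough attribution of productivity loss does not match the instrument named for it.

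Bias in the cost comparison needs a difference in adverse-event cost between the arms. The article gives no basis for expecting one in either direction, so it does not support a claim that one particular medicine will look too cheap. The size cannot be computed from the article. With 15 per arm a single costly event could matter, but that rests on assumed costs.

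Severity is low to moderate. The abstract calls the economic evaluation exploratory, but the repair is cheap and makes the cost-utility ratio coherent.

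**What to change.** In Section 2.9 and the Table 1 footnote:

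1. Define costs as those due to chronic cough or to adverse events of the study drugs.
2. Record the two as separate items on the existing cost questionnaire, including at the Week 24 call. If the questionnaire already asks about adverse-event care, only the wording needs to change.
3. Put both in the base case and report cough-only costs as a sensitivity analysis.
4. Align the productivity wording with the General Health instrument, so that this component is no longer described as due to chronic cough.

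The cost is at most one more item at five contacts already scheduled, plus the wording. The downside is some noise from events of uncertain cause, which the cough-only sensitivity analysis would show. The change is best made before cost data are collected, because costs not asked about at the time may be hard to recover later.
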